### Data collection

Participants will go through four assessment periods at baseline, 6 weeks (post-program), 6 months, and 12 months follow-up. The training and clarification session will be completed by telephone to ensure participants are equipped with the skills to access the intervention contents. Before the first, third and fourth assessment periods, eligibility will be checked against inclusion and exclusion criteria through a telephone screening/re-screening call, 1 week prior to each visit. Participant's timeline is shown in Figure 3.

*Assessment* 1 (baseline): Clarification session about the study. If participants are still interested in enrolling in the study, eligibility will be checked, and they will be asked to fill out an informed consent form. Randomization and allocation to one of the four arms of the trial will be performed. Data on demographics and potential psychological moderators will be collected. A battery of psychological and behavioral questionnaires will be completed online using google forms (in one-week time) – running behavior (i.e. frequency and minutes per week), motivations, basic psychological needs, motives and gains, self-regulation skills, passion, flow, and vitality. This task is estimated to take approximately 1 h, but participants will be able to do breaks and return later to complete the psychometric evaluation during that week. Debrief on how to use the KOR web-based intervention content – the toolkit (approximately 1 h).

*Assessment*s 2 and 3 (intervention's end and 6-month follow-up). Email reminder prior to this evaluation period will be sent. The same battery of psychological and behavioral questionnaires will be completed online using google forms (in one-week time) – running behavior (i.e. frequency and minutes per week), motivations, basic psychological needs, motives and gains, self-regulation skills, passion, flow, and vitality –, and will take approximately 1 h.

*Assessment* 4 (12-month follow-up). Running behavior maintenance will be assessed through a telephone call, asking participants whether they keep running at their initial level or higher, or not.

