### Recruitment and randomization

Part of the runners will be recruited from the PNMC program, which consists in 2–3 supervised running group-sessions of 10–20 runners per week, lasting 90 min each. Certified trainers lead these sessions, apply specific methodologies for running and for walking sessions. Prior to their enrollment, trainers must complete a training course. The other set of runners (which run freely, on their own) will be recruited from the community (recreational runners). To recruit this sample, we will use online advertisement and running events list servers, reach out for running clubs, and partnerships with both state and private organizations.

We will use a rolling recruitment strategy: participants will join the study as soon as they are considered eligible to facilitate management of available human resources. Each set of runners will be randomly assigned to the KoR intervention group or the control group general information group in a 1:1 ratio, stratified by group (PNMC and FRR). The method of randomized permuted blocks will be used, with random block lengths (4 or 6) (Broglio, 2018). Because participants will know which arm of the study they are in, blinding is not possible.

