### Assessments

Data on demographics (age, gender, date of birth, education, income, employment, marital status, weight, height, physical activity history, and personal characteristics) and potential psychological moderators (i.e. index of autonomous functioning) will be collected only at baseline.

The primary outcome of this study is running behavior, which will be measured at baseline, intervention's end and 6-month follow-up by self-report (frequency and minutes of running per week). At 12 months, participants will be asked by telephone whether they keep running (at least) at their initial level, or not.

Secondary outcomes will include putative mediators and outcomes. Basic psychologic need satisfaction will be assessed via the Psychological Need Satisfaction in Exercise Scale (Wilson, Rogers, Rodgers, & Wild, 2006); Basic psychological need frustration will be assessed trough the Basic Psychological Need Frustration in Exercise Scale (Chen et al., 2015); Motives and gains via Exercise Motives and Gains Inventory (Ingledew, Markland, & Strömmer, 2014); Behavioral regulations will be assessed via the Behavioral Regulation in Exercise Questionnaire – 3 (Cid et al., 2018); Self-determination trait will be assessed via the Index of Autonomy Functioning (Weinstein, Przybylski, & Ryan, 2012); Self-regulation skills will be measured trough the Action planning, Coping planning, and Action control scales (Sniehotta, Scholz, & Schwarzer, 2005a; Sniehotta, Schwarzer, Scholz, & Schuz, 2005b); Self-efficacy will be assessed via the Modified Bandura's Exercise Self-Efficacy Scale (Bandura, 1997); Automaticity will be measured trough the Self-Report Behavioural Automaticity Index (Gardner & Tang, 2014; Gardner, Abraham, Lally, & de Bruijn, 2012); and exercise identity via the Exercise Identity Scale (Anderson & Cychosz, 1994). Regarding psychological outcomes, flow will be measured through the Dispositional Flow Scale – 2 in Exercise (Jackson & Eklund, 2002); Vitality will be assessed through the Subjective Vitality Scale (Ryan & Frederick, 1997); and passion through the Passion Scale (Cid et al., 2019).

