### Analytical strategy

Statistical analysis will be performed using SPSS Statistics version 25.0 (SPSS Inc., an IBM Company, Chicago IL, USA). Descriptive statistics will be calculated (mean, standard deviation and range). Repeated measures with Bonferroni corrections for adjusted comparisons will be used to examine differences between each intervention group(PNMC or SRM) and controls (i.e. free recreational runners), at all assessment points, in the primary and secondary outcomes measured. Statistical significance will be set at *p* < 0.05.

Mediation analysis, will test the psychological mechanisms underlying changes in running behavior from baseline to post program, 6 and 12 months. Multilevel modeling will be used to determine the SRM intervention effect on these motivational variables, with intervention group (SRM vs. Control group) as the between-subject factor and change in self-regulation and competence for running at baseline, 6–8 weeks, 6months and 12 months, serving as dependent variables. If necessary, multiple imputation methods will be implemented to provide robust results for primary and main secondary outcomes.

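### Assessment 1 places randomisation before the self-reported baseline battery and does not say the arm is withheld until the battery is submitted, so the baseline can be answered with knowledge of allocation

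*Protocol article*

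**What the plan says.** The Data collection section describes Assessment 1 in this order: clarification session, eligibility check, informed consent, randomisation, demographics and moderators, questionnaire battery, toolkit debrief. The steps that matter here are:

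- Allocation and the first data: "Randomization and allocation to one of the four arms of the trial will be performed. Data on demographics and potential psychological moderators will be collected".
- The battery: "A battery of psychological and behavioral questionnaires will be completed online using google forms (in one-week time"). It covers running frequency and minutes, motivation, psychological needs, self-regulation skills, passion, flow and vitality. It takes about 1 h, and "participants will be able to do breaks and return later to complete the psychometric evaluation during that week".
- The last listed step: "Debrief on how to use the KOR web-based intervention content – the toolkit (approximately 1 h").

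On blinding, the Recruitment and randomization section says: "Because participants will know which arm of the study they are in, blinding is not possible". Allocation is 1:1 between the KOR intervention and general information, stratified by PNMC and FRR.

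The Assessments section says that the primary outcome, running behaviour, is "measured at baseline, intervention's end and 6-month follow-up by self-report (frequency and minutes of running per week"). In the Analytical strategy section, the mediation analysis concerns "changes in running behavior from baseline to post program, 6 and 12 months", and the multilevel model uses change in self-regulation and competence. The Discussion also names change in running behaviour as a dependent variable.

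**The concern.** In an open trial with self-reported outcomes, the baseline is protected only if it is recorded before participants can learn their arm. Here the written order puts allocation first, and the battery can still be open a week later. Someone who knows they will receive a programme on motivation and self-regulation may rate current running, motivation or planning differently from someone who knows they will not. If so, the two randomised groups no longer share an unaffected starting point, and analyses that measure change from that point carry the difference into the treatment estimate. Adjusting for such a baseline does not repair this and can itself add bias.

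The order also decides how non-return of the battery counts. A person who consents and never submits it has already been randomised, so the loss falls after randomisation and can differ by arm.

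**Working it through.** The document states no figure for this point, so there is nothing to reproduce. The check has two parts.

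**1. Order and safeguards**

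| Question | What the protocol article gives | Where |
|---|---|---|
| When is allocation done? | After consent, ahead of demographics, moderators and battery | Data collection, Assessment 1 |
| How long is the battery open afterwards? | Up to one week, with breaks | Data collection, Assessment 1 |
| Are participants blinded? | No | Recruitment and randomization |
| Is the arm withheld until the battery is submitted? | Not stated anywhere | – |
| Is the baseline self-reported? | Yes | Assessments |
| Is baseline a reference for change? | Yes, in the mediation analysis and as a named dependent variable | Analytical strategy; Discussion |

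The text therefore allows a participant to complete the baseline knowing the arm.

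**2. What a baseline shift would do**

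Let δ be the true standardised effect, b the amount (in SD) by which knowing the arm raises the SRM group's reported baseline relative to its comparator, p the fraction of that shift still present at follow-up, and ρ the correlation between baseline and follow-up (equal SDs assumed).

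- Change-score contrast: δ + pb − b = δ − (1 − p)b
- Baseline-adjusted contrast: δ + pb − ρb = δ − (ρ − p)b
- Follow-up values alone: δ + pb

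With p = 0 the biases are −b, −ρb and 0. The follow-up contrast is then clean, and using the baseline is what brings the bias in.

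The one input from the document is δ = 0.23 (Power calculations and sample size estimation). The values of b, ρ = 0.5 and p = 0 are assumptions, because the article gives none of them.

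| b (assumed) | True 0.23, SRM baseline shifted up: change score | Same, adjusted (ρ = 0.5) | True 0, SRM baseline shifted down: change score | Same, adjusted (ρ = 0.5) |
|---|---|---|---|---|
| 0.05 | 0.23 − 0.05 = 0.18 | 0.23 − 0.025 = 0.205 | 0.05 | 0.025 |
| 0.10 | 0.13 | 0.18 | 0.10 | 0.05 |
| 0.15 | 0.08 | 0.155 | 0.15 | 0.075 |
| 0.20 | 0.03 | 0.13 | 0.20 | 0.10 |

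The table shows sensitivity only. It is not an estimate of bias in this trial. If the shift persisted in full (p = 1), the change-score bias would be (1 − 1)b = 0.

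**The case against.** The strongest reply is that the article never gives the moment of disclosure. It says allocation is performed, not that participants are then told. The step that would plainly reveal an SRM allocation, the toolkit debrief, is listed after the battery. The participant timeline figure is not available to check, and an article may condense a fuller protocol. All of that stands: a reader might infer that participants definitely know their arm before answering, and the text does not establish it. What survives is that the only order given puts allocation first, the trial is open, and no safeguard is stated.

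A second reply is that the same self-report battery is used under the same open allocation at later assessments, so a shift that persists cancels in a change score. This is correct, and it limits the formula to the part of the shift that does not persist.

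A third is that loss between allocation and baseline is hypothetical. All 18 pilot participants completed the baseline assessment. This is fair evidence, but the pilot was not randomised, so it does not test what people do once they know their arm. In the same pilot, 83.3% found the questionnaire too long, and 7 completed it after the programme although 15 finished the intervention.

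A fourth is that the primary outcome is defined as running at each time point, not as change, and that no covariate adjustment is specified. This is also correct. The concern bears on the analyses that do use change, and on any contrast that uses the baseline as one of its measurements.

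**Conclusion.** The point holds as a weakness in the written sequence. Assessment 1 allows a self-reported baseline to be given with knowledge of the arm. This could bias the randomised SRM versus no-SRM contrast within PNMC and within FRR, and it makes non-return of the battery a post-randomisation loss. It does not extend to PNMC versus FRR, because that membership is not randomised and participants know it anyway.

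Neither the direction nor the size can be found from the document. What can be said is that a non-persisting shift of b SD moves a change-score contrast by b, and that the expected effect of 0.23 is small enough for modest shifts to matter.

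Three stronger readings are tempting, and the document does not support them:

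- **SRM participants use the toolkit before answering.** The debrief is listed after the battery, and nothing indicates earlier access.
- **The 12-month maintenance outcome is distorted as well.** At that point "participants will be asked by telephone whether they keep running (at least) at their initial level, or not". Nothing ties this level to the questionnaire value, so a shift in that value need not affect the answer.
- **The bias is a known share of the target effect in minutes per week.** That would need an SD for running minutes and a size for the shift, and the article gives neither.

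**What to change.** Reorder Assessment 1 as follows: eligibility, consent, completed baseline battery received (with the running item required), randomisation and disclosure of the arm, toolkit debrief.

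The change resequences existing steps and adds no procedure. Randomisation is delayed by up to one week per participant, and people who do not return the battery are lost before randomisation instead of after it. It cannot be applied retrospectively to anyone already enrolled.

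If disclosure already follows submission in practice, one sentence saying so would answer the reporting concern. Participants who never return the battery would still be post-randomisation losses, so the full reordering is preferable.

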### Analytical strategy

Statistical analysis will be performed using SPSS Statistics version 25.0 (SPSS Inc., an IBM Company, Chicago IL, USA). Descriptive statistics will be calculated (mean, standard deviation and range). Repeated measures with Bonferroni corrections for adjusted comparisons will be used to examine differences between each intervention group(PNMC or SRM) and controls (i.e. free recreational runners), at all assessment points, in the primary and secondary outcomes measured. Statistical significance will be set at *p* < 0.05.

Mediation analysis, will test the psychological mechanisms underlying changes in running behavior from baseline to post program, 6 and 12 months. Multilevel modeling will be used to determine the SRM intervention effect on these motivational variables, with intervention group (SRM vs. Control group) as the between-subject factor and change in self-regulation and competence for running at baseline, 6–8 weeks, 6months and 12 months, serving as dependent variables. If necessary, multiple imputation methods will be implemented to provide robust results for primary and main secondary outcomes.

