### Power calculations and sample size estimation

Two types of sample size calculations were made: (a) using the primary outcome – running minutes and (b) using secondary outcomes, in particular, changes on key psychosocial variables. Regarding our primary outcome, we have used vigorous physical activity for our calculations. A small effect size (Cohen's *d *= 0.23) is expected, a value previously registered in studies with intrinsic motivation interventions (Ntoumanis et al., 2020; Sheeran et al., 2020). Considering a power of 0.8 with two-tailed analysis, we estimated that each intervention group should have 37 (*p *= 0.05) or 55 participants (*p *= 0.01). Concerning our secondary outcomes, we are expecting effects sizes ranging from 0.23 to 0.73, based on previous reports (Ntoumanis et al., 2020; Sheeran et al., 2020). Thus, assuming an effect size of 0.50, 18 subjects/group will be required to detect significant differences at *p *= 0.05 and 28 for *p *= 0.01. Given that the primary outcome is expected to have a smaller effect size, and expecting a dropout rate of 15% at follow-up, we estimate that approximately 55 subjects/group are needed at baseline (for *p *= 0.05). Thus, recruiting 220 participants will ensure high statistical power for our primary analyses, extending its power to the secondary analyses.

Trial results will be published in peer-reviewed scientific journals and in several international and national scientific conferences. The website will be our central media to promote the dissemination of the results to the general public. Other media will be reached through university partners and website.

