## Discussion

This paper presents the rationale, development, study design, methods and pilot application of the KOR trial, aimed at testing the effect of the intervention on the maintenance of recreational running behavior over time, after being voluntarily initiated by community-dwelling adults in the previous 3 months. This ‘light-touch’ intervention is unique in that it approaches running behavior and its sustainability, delivered in a digital format, and based on strong theoretical foundations.

We hypothesize that the sustainability of running behaviors will be higher in the SRM groups compared to the control group. Change in running behavior (e.g. frequency and minutes of running per week) and secondary outcomes related to the quality of the running experience (e.g. passion, flow, vitality) will be used as the dependent variables.

Additionally, the results of the pilot feasibility study, intended at testing intervention adherence, participant satisfaction, and questionnaire acceptance, were also presented. Overall, the pilot study indicated that the intervention has good acceptability, feedback was very positive, but toolkit interaction decreased after the first weeks, which is common in web-based interventions (Baumel & Yom-Tov, 2018). Moreover, the generalized use of other running-related devices, applications and communities may have overlapped with the anticipated content of the toolkit, challenging participants’ interaction. The completion ratio of the post-program questionnaire was low, maybe due to its extension and burden, but also because its timeline ended near the summer break.

The main trial should reduce questionnaire length and burden, and include interface with usual monitoring gadgets and apps (APIs), to increase data detail and prevent ‘unnecessary’ data insertion by the participants. Features such as feedback and social sharing, added to the goal setting features already integrated in the toolkit, may also increase attractiveness (Hosseinpour & Terlutter, 2019).

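### On its plain reading, the Bonferroni rule makes the randomised SRM contrast share its 5% with the non-randomised PNMC contrast: valid, but inefficient

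*Protocol article*

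**What the plan says.** Under Analytical strategy the article states: "Repeated measures with Bonferroni corrections for adjusted comparisons will be used to examine differences between each intervention group(PNMC or SRM) and controls". Controls are there described as the free recreational runners. The same sentence extends the comparisons to cover groups "at all assessment points, in the primary and secondary outcomes measured". The overall level follows: "Statistical significance will be set at" p < 0.05. No divisor is given, and the family over which it applies is not defined.

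Under Recruitment and randomization, each set of runners is allocated to the KoR intervention or general information "in a 1:1 ratio, stratified by group (PNMC and FRR"). PNMC runners come from an existing programme and free runners (FRR) from the community, so PNMC status is a recruitment stratum.

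The directional hypothesis about running, in the Discussion, concerns SRM: "We hypothesize that the sustainability of running behaviors will be higher in the SRM groups compared to the control group". PNMC versus FRR is nevertheless a declared comparison; Study design lists it first of three.

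The sample-size section works at p = 0.05 (with a 0.01 alternative) and mentions no Bonferroni allowance.

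**The concern.** The sentence attaches Bonferroni to two named group comparisons. If both are in one family, the contrast that randomisation protects gives up half of its alpha, or more, to a contrast that remains open to selection however alpha is divided. Runners who joined an organised programme may differ from those who run alone, and a stricter threshold does not change that.

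What is at stake is power on the trial's main question: a real SRM effect is more likely to be declared non-significant. An ordered test would keep the same familywise protection for these two contrasts without that loss. Even where several tests must share alpha, Holm protects the familywise error as well as Bonferroni does and is never less powerful.

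**Working it through.** **Inputs from the article.** Overall alpha 0.05, two-sided, 80% power ("Considering a power of 0.8 with two-tailed analysis"); primary-outcome effect d = 0.23, which "is expected, a value previously registered in studies with intrinsic motivation interventions"; 37 per group at 0.05 and 55 at 0.01; 55 per group recruited; 15% dropout.

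**Assumptions.** The number of group comparisons m is not stated; 2 is the minimum on the plain reading, and 3 and 6 are shown for range. Pooling SRM over the two strata is also an assumption.

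**1. The plan's own sample size.** The article says "we estimated that each intervention group should have 37" at p = 0.05. For two means, n per group = 2(z(1−α/2) + z(power))² / d².
- α = 0.05: 2 × (1.960 + 0.842)² / 0.23² ≈ 297, against the stated 37.
- α = 0.01: about 442, against the stated 55.

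The stated figures are not reproduced. That is a separate problem, and the next step does not depend on it.

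**2. Cost of Bonferroni as a share of the sample.** At a given power, cost = 1 − [(z(1−0.05/2) + z(power)) / (z(1−0.05/(2m)) + z(power))]². No effect size enters.
- m = 2, 80% power: 1 − (1.960 + 0.842)² / (2.241 + 0.842)² = 17.4%.
- m = 3, 80% power: 25.0%. m = 6, 80% power: 35.2%.
- m = 2 at other powers: 15.3% at 90%, 19.3% at 70%, 23.5% at 50%.

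In sample terms at d = 0.23, 80% power needs 297 per group at 0.05 and 360 at 0.025; 1 − 297/360 = 17.5%. At a fixed sample, a test with 80% power at 0.05 has 71.2% at 0.025.

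**3. Power at the planned size and the protocol's d = 0.23.** Completers per group: 55 × 0.85 = 46.75. Pooled over strata: 2 × 46.75 = 93.5 per side. Power ≈ Φ(d√(n/2) − z(1−α/2)).
- Pooled: 0.23 × √(93.5/2) = 1.573. At 0.05, Φ(1.573 − 1.960) = 34.9%. At 0.025, Φ(1.573 − 2.241) = 25.2%.
- One stratum only (46.75 per group): 19.8% falls to 12.9%.

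**4. Power on the protocol's own scale.** Take 37 per group as giving 80% at 0.05.
- With 46.75 completers, power is 88.3% at 0.05 and 81.8% at 0.025.
- The number needed at 0.025 is 37 × (3.083/2.802)² ≈ 45.

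On that scale the nominal 80% survives, but the scale does not match d = 0.23 (step 1).

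**The case against.** The strongest reply is that the sharing of alpha is inferred. The sentence covers groups, assessment points and outcomes together and gives no divisor. Correction across time points within each contrast also fits it, and SRM would then share nothing with PNMC. This stands as a condition on the finding. The plain reading remains the group comparisons, because those are what the sentence names.

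Second, PNMC versus FRR is not incidental. Organised versus free running is one of the two design conditions in Study design, and correcting over two declared comparisons is valid and conservative. This also stands. Lack of randomisation limits what the PNMC contrast can show; it does not make including it in the family an error.

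Third, on the protocol's own planning figures the intended 80% is kept (81.8%). The arithmetic is right, but it rests on the 37 per group that d = 0.23 does not give.

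Fourth, testing SRM alone at 0.05 presupposes one primary test. The Assessments section defines running behaviour by both frequency and minutes, at intervention end and 6 months, with a yes/no question at 12 months. This stands, and the fix has to settle it first.

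A reader might take 17% as a floor. It is not: it assumes two comparisons and 80% power, and falls to about 15% at 90% power. A reader might also take the phrase under Data collection about allocation to one of four arms to mean that PNMC is randomised; the recruitment section shows that it is not.

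**Conclusion.** The point holds as a conditional loss of efficiency. If the Bonferroni family contains at least the SRM and PNMC comparisons with controls, the SRM contrast is tested at 0.025 or lower. With exactly two comparisons and 80% power, the loss equals about 17% of the sample. At d = 0.23 with SRM pooled over strata, power drops by about ten percentage points, from 35% to 25%. If the correction runs only across time points within each contrast, the loss attributed to PNMC is zero.

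It would be tempting to say that the analysis is wrong or that false-positive error is inflated. The document supports neither: Bonferroni controls the familywise error here and errs on the conservative side. The case for change is that a rule with equal protection and more power for the randomised question is available at almost no cost.

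**What to change.** Settle the following in the analysis plan before any outcome data are seen:

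1. Name one primary running measure and one primary time point.
2. Test the randomised contrast, SRM versus no SRM, on that measure first, at two-sided 0.05. State whether it is pooled over the PNMC and FRR strata.
3. Then test PNMC versus FRR in fixed sequence, or report it as an observational estimate with a confidence interval.
4. Wherever several comparisons (groups, time points or measures) remain in one family, define the family and use Holm in place of Bonferroni.

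The cost is wording, with a small downside. PNMC versus FRR, a declared aim, would be tested only if SRM succeeds, or would lose confirmatory status. Holm also gives less simple simultaneous intervals than Bonferroni. No participants are added. The change does not repair the sample size: at d = 0.23, even the full 0.05 leaves the pooled SRM test at about 35% power, and that needs separate attention.

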### The case for recreational running

Running is one of the most popular forms of leisure-time exercise (Andersen, 2020; Running-USA, 2020; Teixeira, Marques, Lopes, Sardinha, & Mota, 2019) in part because it is inexpensive and can be performed anywhere, almost at any time. In addition, it requires little technical skills, is relatively safe, and it is easy to learn. The health benefits of running are vast, including prevention of obesity, hypertension, dyslipidemia, type 2 diabetes, osteoarthritis and hip replacement, benign prostatic hypertrophy, respiratory disease, cancer, disability, reduction of cardiovascular, and all-cause mortality (Lavie et al., 2015; Lee et al., 2014; Pedisic et al., 2019).

Running stimulates the interest of the research community, especially because of the long hours of training throughout the year and the large number of events runners participate in (Zach et al., 2017). This suggests that motivational aspects related with training for and completing a race may be unique (Zach et al., 2017). With this in mind, running clubs/groups may provide a novel testbed for understanding why people adopt recreational running and how motivational factors can support PA maintenance.

To better promote running sustainability and its long-term health benefits, it is crucial to understand individuals’ running experiences and outcomes, as well as the factors that predispose them to engage in this activity. Studying the antecedents and outcomes of running motivation, as well as the efficacy of different types of interventions to promote running behavior will enhance the understanding of the phenomenon, possibly creating new insights into the effective promotion of PA maintenance.

To our knowledge, no previous study has been designed to test the efficacy of interventions to promote sustained running behavior and identify the mechanisms behind it. Future interventions will aim to test if motivation and self-regulation mediators can be successfully modified via a digital-based intervention. This will ultimately lead to sustained adherence to an activity that participants have chosen and appear to enjoy, via large-reach interventions, capitalizing on the widespread availability of running clubs/events and increased reliance of exercisers on remote technologies.

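### The baseline-to-post-program mediation test measures mediators and running in the same battery, so it cannot show which drives which; it should be labelled associational and joined by a time-ordered analysis

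*Protocol article*

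**What the plan says.** Analytical strategy commits to mediation over three intervals: "Mediation analysis, will test the psychological mechanisms underlying changes in running behavior from baseline to post program, 6 and 12 months". The psychological scales are given this role under Assessments: "Secondary outcomes will include putative mediators and outcomes".

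Data collection sets the schedule: "Participants will go through four assessment periods at baseline, 6 weeks (post-program), 6 months, and 12 months follow-up". Nothing is scheduled between baseline and 6 weeks. For the 6-week and 6-month assessments it says "The same battery of psychological and behavioral questionnaires will be completed online using google forms", to be finished within one week, and lists the content as "running behavior (i.e. frequency and minutes per week), motivations, basic psychological needs, motives and gains, self-regulation skills, passion, flow, and vitality". Running and the candidate mediators thus come from one self-report session or week.

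At 12 months, Data collection describes only a telephone question on whether the participant still runs at the initial level or above. No psychological scales are listed. Analytical strategy nevertheless names self-regulation and competence at 12 months among its dependent variables. The two sections need to be reconciled.

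**The concern.** A mediation claim needs the mediator to change before the outcome does. From baseline to post program there are two measurement points, and both variables are taken at each. A baseline mediator cannot carry an effect of the intervention, so the 6-week mediator has to be used, and it is concurrent with 6-week running.

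The reverse path is plausible here. People who keep running may report more competence, stronger self-regulation and greater gains because they kept running. Participants also know their arm (Recruitment and randomization says blinding is not possible), so arm-related reporting could move both self-reports together. A concurrent model counts either process as mediation.

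At stake is a reported psychological mechanism that does not operate. A fuller analysis plan could not repair this leg, because no choice of model creates a time order from two shared measurement points.

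**Working it through.** The document gives no mediation figure to reproduce. The check has two parts.

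**1. Schedule against analysis**

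| Running interval | Post-randomisation mediator data available | Time order |
|---|---|---|
| Baseline to post program | 6 weeks only, same battery as the outcome | None possible |
| Baseline to 6 months | 6 weeks (earlier) or 6 months (same battery) | Not fixed by the text |
| Baseline to 12 months | 6 weeks or 6 months; no scales at 12 months | Lagged by necessity |

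**2. Size of a spurious result**

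Inputs from the document: expected effect d = 0.23 for the primary outcome; 55 participants per group and 220 in total (Power calculations and sample size estimation). This gives n = 110 for an intervention-against-no-intervention comparison in one runner stratum, and n = 220 overall.

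Assumptions, not in the document: residual SDs of 1; running raises the mediator by g = 0.2 to 0.4 SD per SD; 6-month running = 0.6 × 6-week running + error; no mediator effect on running. Scores are treated as already adjusted for baseline.

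Model: Y6w = 0.23·T + e; M6w = g·Y6w + u.

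- Arm-to-mediator path: a = 0.23·g.
- Mediator-to-running path given arm: b = g/(1 + g²).
- Spurious indirect effect: a·b = 0.23·g²/(1 + g²).
- Spurious share of the total effect: g²/(1 + g²).

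For g = 0.2: share 0.04/1.04 = 3.8%, indirect effect 0.23 × 0.038 = 0.009 SD. For g = 0.4: share 0.16/1.16 = 13.8%, indirect effect 0.23 × 0.138 = 0.032 SD. The true value is 0 in both cases.

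Simulation of the same model (10,000 trials per row, two-sided 0.05):

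| n | g | Path b significant | Both paths significant |
|---|---|---|---|
| 110 | 0.2 | 53% | 3.1% |
| 110 | 0.4 | 98% | 7.2% |
| 220 | 0.2 | 83% | 5.0% |
| 220 | 0.4 | 100% | 9.5% |

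**3. What a lag does**

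Running drives the mediator, true mediation 0%, outcome 6-month running:
- Without adjustment for 6-week running: path b = 0.6·g/(1 + g²) and total effect 0.6 × 0.23, so the share is again g²/(1 + g²), about 4% to 14%. A lag alone does not remove the reverse path.
- With that adjustment: about 0%, with path b significant in about 5% of trials.

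The mediator drives running within the programme, true mediation 100% (assumed arm-to-mediator effect 0.5; mediator-to-6-week-running effect 0.2 or 0.4; 6-month running = 0.6 × 6-week running + error):
- Without adjustment for 6-week running: about 100% mediated.
- With adjustment: about 0% mediated.

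The adjusted lagged model therefore returns about 0% in both worlds.

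**The case against.** The strongest reply is that Analytical strategy fixes the interval for the change in running only. It does not say which mediator time point is used or which covariates enter, and an article commonly leaves such detail to the full analysis plan. This stands for the 6-month leg. A reader might infer that the whole mediation analysis is same-visit; the document does not support that, and the 12-month leg cannot be same-visit on the stated schedule. The reply fails for the post-program leg, where only one post-randomisation mediator measurement exists.

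Second, mechanism is not a primary claim. The phrase "identify the mechanisms behind it" occurs in a sentence about what earlier studies have not done, and the mediators are listed with the secondary outcomes. This stands and limits the weight of the point. Even so, the mediation sentence uses the language of testing mechanisms, which the post-program leg cannot support.

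Third, the numbers are modest. A reader might take the 53% to 100% for path b as a false-mediation rate. It is not: a mediation finding needs both paths, and the joint rate is about 3% to 9.5%, held down by low power on the arm-to-mediator path.

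Fourth, a reader might conclude that a lagged model adjusted for 6-week running should be the sole main analysis. The second scenario above rules that out, since this model hides mediation that has already acted through running by 6 weeks, the period in which the toolkit is delivered.

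**Conclusion.** The point holds for the baseline-to-post-program leg. As scheduled, that leg describes an association between concurrent changes and cannot support a directional mechanism. It does not extend to the 6-month leg, whose pairing is open, or to the 12-month leg, which is lagged. Nor does it show that the plan as a whole will report a false mechanism.

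Under the stated assumptions, the spurious share is about 4% to 14% of a 0.23 SD effect, with both paths falsely significant in about 3% to 9.5% of trials. These figures depend on the assumed g. Correlated reporting error would add to the bias and is not included; unadjusted change scores would be noisier and would lower the path-b detection rate. The randomised comparisons of running are not touched.

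**What to change.** - Report the baseline-to-post-program mediation result as a same-time association only.
- Add a time-ordered analysis: arm to 6-week mediator to 6-month running, adjusted for baseline mediator and baseline running. Show it both with and without adjustment for 6-week running.
- Add the 12-month yes/no status as a later outcome, using a mediation method for binary outcomes.
- State which mediator time point is paired with each running time point, and reconcile the 12-month mediators named in Analytical strategy with the telephone-only 12-month contact in Data collection.
- State the limits beside the results. Adjusting for 6-week running excludes mediation already expressed in running by then; omitting it leaves reverse causation open; unmeasured confounding between mediator and running remains either way, because the mediator is not randomised.

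The cost is analysis wording and a few extra models. The measurements used are already planned. The post-program result loses its causal label, and the two lagged versions may disagree, in which case the mechanism stays unresolved.
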